## Abstract

Background: Heart failure is a burgeoning disease that imposes an enormous social and economic burden globally. It presents a significant public health challenge due to its high morbidity and mortality. In recent years, notable advancements have been made in the pharmacological treatment of heart failure with reduced ejection fraction (HFrEF), with guideline-directed medical therapy (GDMT) emerging as the cornerstone of HFrEF management. Although the angiotensin-receptor neprilysin inhibitor (ARNI), sacubitril/valsartan, is recognized as an integral component of HFrEF pharmacotherapy, variations in dose response have been observed in the Indian population. Furthermore, substantial differences exist in heart failure management practices across various types of hospitals in India. To address this paucity, the Assessing the Dosage Pattern and Demographic Characteristics in Heart Failure Reduced Ejection Fraction Patients Initiated with Angiotensin Receptor-Neprilysin Inhibitor in India (ADD-ARNI) study was designed to characterize contemporary HFrEF pharmacotherapy in India. This is a prospective, multicenter observational study to evaluate the dosage patterns, treatment adherence, and safety of ARNI therapy in HFrEF patients in India.

Methods: The ADD-ARNI study is a prospective, multicenter, observational study designed to enroll 3000 patients diagnosed with HFrEF. The study population will consist of symptomatic chronic HFrEF patients who are eligible for the initiation of sacubitril/valsartan (ARNI) as per the clinical judgement of the treating physician. The primary endpoint of the study is the dosage pattern of sacubitril/valsartan at the start as well as the end of the study. The secondary endpoints include the dosing pattern of other concomitant HFrEF medications at the start and end of the study, such as the doses of beta-blockers (BB), mineralocorticoid receptor antagonists (MRA), sodium-glucose cotransporter 2 inhibitors (SGLT2i), and diuretics, the implementation of GDMT at the end of the study, the assessment of the effectiveness of sacubitril/valsartan therapy based on changes in functional capacity and N-terminal pro-B-type natriuretic peptide (NT-proBNP) levels from baseline to follow-up, and the incidence of adverse events, either spontaneously reported by the patients or noticed by the clinician during the study.

Conclusion: In heart failure management, there is an unmet clinical need to gain insights about the real-world evidence of pharmacotherapy, adherence to current practice guidelines, and impact on clinical outcomes. Undertreatment with doses less than 50% of the guideline-recommended target doses is associated with poorer prognosis. The ADD-ARNI study will provide real-world evidence on dosage patterns, effectiveness, treatment persistence, safety, and implementation of GDMT among Indian HFrEF patients treated with sacubitril/valsartan therapy.

## Introduction

Heart failure (HF) is a multifaceted clinical syndrome typically resulting in impaired ventricular blood filling or ejection and is estimated to impact about 56.19 million individuals globally [1,2]. It represents a major public health concern due to its high rates of morbidity and mortality [3]. In-hospital mortality rates remain high at 4-6%, while mortality during the three-month vulnerable phase post-discharge is reported at 10-30%. Mortality among chronic HF patients is as high as 50% in five years following diagnosis [4]. The current estimated incidence of HF in India ranges from 0.7 to 1.5 per 1000 persons per year [5]. The age-standardized prevalence rate of HF in India has increased from 390.4 (1990) to 406.2 (2019) per 100,000 population over the last two decades [6]. 

Study rationale

According to data from the Trivandrum Heart Failure Registry, three out of four HF patients present with heart failure with reduced ejection fraction (HFrEF) [7]. Similar findings highlighting the greater prevalence of HFrEF have been reported by some of the Indian HF registries, including the Medanta registry [8], Cardiology Society of India-Kerala Acute Heart Failure Registry (CSI-KHFR) [9], Indian Council of Medical Research National Heart Failure Registry (ICMR-NHFR) [2], and Indian College of Cardiology National Heart Failure Registry (ICC-NHFR) [10].

Over the past three decades, substantial progress has been made in the pharmacological management of HFrEF [11], and guideline-directed medical therapy (GDMT) has emerged as the standard of care for managing HF [12]. Clinical trials have consistently shown the efficacy of GDMT, which includes beta-blockers (BB), renin-angiotensin system antagonists (such as angiotensin-converting enzyme inhibitors (ACEIs), angiotensin receptor blockers (ARBs), and angiotensin receptor-neprilysin inhibitors (ARNIs)), mineralocorticoid receptor antagonists (MRA), and sodium-glucose cotransporter 2 inhibitors (SGLT2i) [13-15]. These therapies have demonstrated improved cardiac function, enhanced quality of life and functional status, and significantly reduced risks of hospitalization and mortality in patients with HFrEF [12]. Thus, the major clinical guidelines for the management of HFrEF strongly recommend the initiation of GDMT [16]. However, according to the Change the Management of Patients with Heart Failure (CHAMP-HF) registry, the implementation of GDMT in routine clinical practice is significantly varied [17]. The Trivandrum Heart Failure Registry data revealed that only 19% of HFrEF patients on admission and 25% of those during discharge were receiving GDMT, raising concerns about adherence to disease-modifying therapy in India compared to prior published cohorts. Data from other Indian HF registries also reflect a similar trend of underutilization of GDMT [2,9,10,18]. Additionally, Indian patients had worse outcomes, with the 90-day mortality rate of 18.1% in the Trivandrum Heart Failure Registry at least twice as high as that of reported mortality rates published elsewhere [7].

Sacubitril-valsartan, the first class of ARNI, has been shown to significantly reduce mortality as well as hospitalizations and rehospitalizations in patients with HFrEF [19]. Although sacubitril-valsartan is recognized as an integral treatment for HF based on clinical trials, there is limited real-world data on its usage and clinical experience, the implementation of GDMT, and the characteristics of HFrEF patients in the Indian context. Additionally, there is limited clarity on the initiation and up-titration regimen of ARNI in routine clinical practice due to concerns about tolerability, particularly the risk of hypotension [20,21].

To address this gap, the Assessing the Dosage Pattern and Demographic Characteristics in Heart Failure Reduced Ejection Fraction Patients Initiated with Angiotensin Receptor-Neprilysin Inhibitor in India (ADD-ARNI) study is a first-of-its-kind prospective, multicenter observational study designed to evaluate the dosage patterns and treatment persistence of ARNI therapy in patients with HFrEF in India.

## Materials and methods

Study design

The ADD-ARNI study (trial registration number: CTRI/2024/07/071165) is a prospective, multicenter, observational study being conducted at 200 sites across India from September 2024 and is expected to be completed by June 2025. The primary objective of this study is to assess the dosage pattern and treatment persistence of ARNI therapy in patients with HFrEF in India. The secondary objectives are to describe the medication dosage pattern and the implementation of GDMT in patients with HFrEF initiated on ARNI therapy and to evaluate its safety and effectiveness. This study was approved by the Suraksha Institutional Ethics Committee (approval number: N/A) and is being conducted in accordance with the principles of the Declaration of Helsinki, Indian Council of Medical Research (ICMR), International Conference on Harmonization (ICH), Good Clinical Practice (GCP) guidelines, and applicable legislations. The overall study design of the ADD-ARNI study is depicted in Figure 1.

**Figure 1 FIG1:**
[figure not shown]
Flowchart of the study ARNI: angiotensin receptor-neprilysin inhibitor; GDMT: guideline-directed medical therapy; NT-proBNP: N-terminal pro-B-type natriuretic peptide; NYHA: New York Heart Association Original figures are created by the authors and are not adapted from any other sources.

Study population

The study population will consist of symptomatic chronic HFrEF patients as per the European Society of Cardiology (ESC) 2016 criteria [22] and who are eligible for the initiation of sacubitril/valsartan tablets as per the judgement of the treating physician. Patients who are recently diagnosed with HFrEF or chronic HFrEF patients with left ventricular ejection fraction (LVEF) ≤40% and documented for not more than three months, who are stable, and who have not been hospitalized for the past one month prior to enrolment in the study shall be included. Written informed consent shall be obtained from all participants prior to their inclusion in the study. Patients who were deemed ineligible included pregnant and lactating women, patients with acute decompensated HF, patients with hyperkalemia (serum potassium level ≥5.30 mmol/L) within the past two weeks, and patients participating in any other clinical study. Patients should meet all the inclusion criteria and none of the exclusion criteria prior to being enrolled in the study.

Study treatment, duration, and endpoints

Study participants who meet all the inclusion criteria and are deemed eligible for the initiation of ARNI therapy as per the clinical judgement of the treating physician will be initiated on ARNI therapy as per routine clinical practice. This is an observational study that will be conducted over a period of 12 weeks±4 weeks from the date of enrolment of the patient.

The primary endpoint of the study is the dosage pattern of ARNI at the start and end of the study. The secondary endpoints include the HFrEF medication dosing pattern at the start and end of the study with regard to the doses of BB, MRA, SGLT2i, and diuretics, the implementation of GDMT at the end of the study, the assessment of the effectiveness of ARNI therapy based on changes in New York Heart Association (NYHA) functional class and N-terminal pro-B-type natriuretic peptide (NT-proBNP) levels from baseline to follow-up, and the incidence of adverse events, either spontaneously reported by the patients or noticed by the clinician during the study.

Data collection

All data required to fulfill the primary and secondary objectives of the study will be captured in an electronic data capture platform. The data related to demographic and clinical characteristics of patients will be collected at baseline. Additionally, the data points with respect to clinical parameters such as vitals, estimated glomerular filtration rate (eGFR), serum creatinine, serum potassium, and NT-proBNP will be recorded at baseline. Medication-related data, including type of medications, dosage, and titration, will be recorded at baseline and at the end of 12±4 weeks. Any incidences of adverse events will be documented during the study period.

Safety reporting

All adverse events will be captured starting from the date of enrolment until the end of the study, regardless of whether or not they are related to the study intervention. Adverse events, not limited to symptomatic hypotension (systolic blood pressure (SBP) ≤100 mmHg with symptoms like dizziness, blurry vision, fainting, fatigue, and unsteadiness), asymptomatic hypotension (SBP ≤90 mmHg with no symptoms), hyperkalemia (serum potassium levels >5.5 mmol/L), impaired renal function (decline in the eGFR of ≥50%), and persistent cough, shall be recorded during follow-up visits along with any additional adverse events [14]. It is the responsibility of the investigator to capture and report the adverse events (serious and non-serious).

Sample size calculation

The list of potential demographic and clinical characteristics, along with the distributions of patients with HFrEF, was extracted from Philip et al. [23] and Pokharel et al. [24]. Expecting a similar distribution of these characteristics in the current study, the minimum required sample sizes were calculated for 5%, 3%, and 2% precision with a 95% confidence interval (CI). In this study, the target patient population is 3,000, and accounting for an estimated ~15% attrition rate, the sample size is set at 3,600.

The following formulas were used for sample size calculation: for prevalence, \begin{document}n=\frac{\left(1.96\right)^{2}p\left(1-p\right)}{d^{2}}\end{document}, while for mean, \begin{document}n=\frac{\left(1.96xSD\right)^{2}}{d^{2}}\end{document}. Here, p means proportion or prevalence; SD, standard deviation; and d, precision. For proportion, d is absolute, but for mean, it is relative to the mean.

Statistical consideration

All statistical tests will be performed using appropriate software, with a two-tailed overall significance level of 0.05. Categorical data (counts and percentages) will be compared between baseline and 12 weeks using the chi-squared test (or any other test deemed appropriate), while numerical data will be compared between the two groups using an unpaired t-test (or any other test deemed appropriate).

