**Figure 2 FIG2:**
[figure not shown]
One-year mortality rates in Asia N=total number of patients for each registry Asian HF: Asian heart failure [28]; ICC-NHFR: Indian College of Cardiology National Heart Failure Registry [10]; Korea HF: Korea heart failure [29]; Medanta HF: Medanta heart failure [8]; THAI-AHF: Thailand-acute heart failure [26]; THFR: Trivandrum Heart Failure Registry [18]; TSOC-HFrEF: Taiwan Society of Cardiology-heart failure with reduced ejection fraction [27] Original figures are created by the authors and are not adapted from any other sources.

For patients with HFrEF, adhering to guideline-recommended therapies and ensuring up-titration to evidence-based doses is a proven strategy to deliver optimal care. This approach plays a critical role in reducing the risk of recurrent HF hospitalizations and cardiovascular mortality [16,30]. The present study will assess persistence with ARNI therapy over a 12-week period, explore the titration to target doses, and identify barriers to achieving these targets.

Evidence from previous studies, such as the CHAMP-HF Registry, evaluated the effectiveness of medical therapy dosing for HF in outpatients with chronic HFrEF. The study found that compared to target dosing, lower dosages and non-use of ACEI/ARB/ARNI and beta-blocker therapies were independently associated with higher mortality rates. Additionally, lower doses of ACEIs/ARBs/ARNIs were associated with an increased risk of HF hospitalizations and a higher five-year mortality [17].

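### As worded, the primary endpoint gives two ARNI dose distributions and their net shift, not the shares of patients titrated up, unchanged, down or stopped

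*Protocol article*

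**What the plan says.** Under *Study treatment, duration, and endpoints*, the article says: "The primary endpoint of the study is the dosage pattern of ARNI at the start and end of the study". The same paragraph words NYHA class and NT-proBNP as changes from baseline to follow-up; the ARNI dose endpoint carries no such wording.

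*Statistical consideration* says: "Categorical data (counts and percentages) will be compared between baseline and 12 weeks using the chi-squared test (or any other test deemed appropriate". For numerical data it names an unpaired t-test between two groups, again with an open alternative.

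Three other places bear on what the endpoint should deliver:

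- *Study design*: "The primary objective of this study is to assess the dosage pattern and treatment persistence of ARNI therapy in patients with HFrEF in India".
- *Discussion*: over the 12 weeks the study will also "explore the titration to target doses, and identify barriers to achieving these targets". The *Introduction* prepares for this by noting that "there is limited clarity on the initiation and up-titration regimen of ARNI in routine clinical practice".
- *Data collection*: "Medication-related data, including type of medications, dosage, and titration, will be recorded at baseline and at the end of 12±4 weeks".

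**The concern.** Titration is a movement within a patient. A dose pattern at the start and a dose pattern at the end are two marginal distributions, and opposite movements offset each other in them. Two similar distributions fit a cohort in which nobody's dose changed. They fit equally well a cohort in which many doses were raised and many lowered. These are different descriptions of ARNI use in practice.

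Persistence has a related gap. It is half of the primary objective, but no listed endpoint measures it. The article does not say whether patients off ARNI at the end stay in the end distribution as a category of their own. Only if they do can the stopped share be read from it.

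**Working it through.** **Inputs from the article.** Target 3,000 patients; about 15% attrition; sample size 3,600; the same patients seen at baseline and at 12±4 weeks. The article gives no starting-dose shares and no titration rates, so all dose shares below are assumptions.

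**The plan's own figure.** 3,000/(1 − 0.15) = 3,530, close to the stated 3,600; 3,600 × 0.85 = 3,060. About 3,000 evaluable patients is therefore consistent with the plan.

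**What two distributions allow.** Take three ordered dose levels.

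- Share up ≤ the smaller of (share starting below the top) and (share ending above the lowest).
- Share down ≤ the smaller of (share starting above the lowest) and (share ending below the top).
- Share up ≥ the rise in the share above the lowest level, and ≥ the rise in the share at the top.

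*Example A: 60/30/10% at both times.* Up ≤ min(90, 40) = 40%; down ≤ min(40, 90) = 40%; the lower bound for each is 0%. The upper bounds are reached if, of the 60% starting lowest, 20 stay, 30 move to the middle and 10 to the top, while the 40% starting higher all end lowest. The lowest level again holds 20 + 40 = 60%.

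*Example B: 60/30/10% to 45/35/20%.* Up ≥ 55 − 40 = 15% and ≤ min(90, 55) = 55%; down is 0% to min(40, 80) = 40%. The upper bounds are reached if, of the 60% starting lowest, 5 stay, 35 go to the middle and 20 to the top, and the other 40% end lowest: 5 + 40 = 45%.

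**Less extreme tables, n = 3,000, with the named chi-squared test.**

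| Start counts | End counts | Up | Down | Chi-squared |
|---|---|---|---|---|
| 1,500/1,050/450 | 1,500/1,050/450 | 0% | 0% | 0 |
| 1,500/1,050/450 | 1,500/1,050/450 | 23.3% | 23.3% | 0 |
| 1,500/1,050/450 | 1,200/1,050/750 | 20.0% | 0% | 108.3 |
| 1,500/1,050/450 | 1,200/1,050/750 | 33.3% | 16.7% | 108.3 |

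For the last two rows: 2 × 150²/1,350 + 2 × 150²/600 = 33.3 + 75.0 = 108.3. The test gives the same result within each pair of rows.

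**When the ambiguity is small.** The share down cannot exceed the share starting above the lowest level. If 90% start lowest, at most 10% can go down. With two levels and nobody starting at the higher one, an end share of 20% fixes the share up at 20%.

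**Attrition.** Assume that 15% leave, all from the lowest level, and that no dose changes. Then 60/30/10% becomes 45/85, 30/85 and 10/85, or about 53/35/12%. The end distribution shifts although nobody was titrated.

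**Precision of per-patient shares.** Half-width = 1.96 × √(p(1 − p)/3,000): ±1.1 points at 10%, ±1.6 at 30%, ±1.8 at 50%. The Abstract speaks of enrolling 3,000. If 15% of those were lost, 2,550 would remain, and the worst case would be 1.96 × √(0.25/2,550) = ±1.9 points.

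**The case against.** The case against is substantial, and much of it stands.

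- The endpoint wording does not exclude a start-by-end table, the tests are left open, and a full protocol or analysis plan, not shown, may already cross-tabulate. That is fair. Still, the article does state the endpoint and name the tests, and both point to separate distributions.
- Titration is not in the primary objective. It appears in the *Introduction* as an evidence gap and in the *Discussion* as an aim. The *Discussion* also contrasts this study with an earlier Indian study of dose titration. So the endpoint does match the dosage-pattern half of the objective. Persistence, the other half, has no endpoint.
- The bounds rest on assumed shares and extreme allocations. True; they show what is not identified, not what is likely.
- Adverse events are collected separately, so tolerability does not rest on the dose distributions. This stands, and a transition table would not show why a dose was lowered either.
- Paired methods such as McNemar or Bowker start from the paired table, whose off-diagonal cells are the movements. Correct, but a marginal-homogeneity result on its own still speaks only to the net shift. The table has to be reported.

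A reader might infer that the study cannot answer its titration question at all. The documents do not support that: dosage and titration are recorded at both visits, and the share at target dose at study end can be read from the end distribution.

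**Conclusion.** The point holds as a weakness in the endpoint definition, not in the design or the data capture. Read as worded and analysed with the named unpaired tests, the primary endpoint shows the net shift in ARNI dose. It leaves the shares titrated up, unchanged, down or stopped unidentified, although the article names titration as an aim and persistence as part of its primary objective.

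The size cannot be fixed from the article. It is 0–40% in each direction under the assumed 60/30/10% at both times, and much less if most patients start at the lowest dose. The conclusion assumes that the full protocol or analysis plan does not already specify a per-patient summary. It is a worthwhile improvement at almost no cost; it does not make the planned dose distributions wrong.

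**What to change.** Define the primary result as a per-patient table of ARNI dose at the start against ARNI status at the end, with stopped as an end category. Report the shares titrated up, unchanged, titrated down and stopped, each with a 95% CI, and state how patients without an end visit are counted. Keep the two dose distributions, including the share at target dose, as supporting description. If a test is wanted, use one for paired data.

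The cost is a change to the endpoint wording and one cross-tabulation. Doses are already recorded at both visits, and the planned sample size is sufficient.

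### The abstract gives 3,000 as the number to enrol, while the methods treat 3,000 as the target before attrition and set enrolment at 3,600

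*Protocol article*

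**What the plan says.** The Methods part of the abstract describes an "observational study designed to enroll 3000 patients diagnosed with HFrEF". It mentions neither attrition nor any other number.

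Under Materials and methods, Sample size calculation, the article states that "the target patient population is 3,000, and accounting for an estimated ~15% attrition rate, the sample size is set at 3,600".

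The same section says that "the minimum required sample sizes were calculated for 5%, 3%, and 2% precision with a 95% confidence interval (CI"). It prints one formula for a prevalence, n = 1.96²·p(1−p)/d², and one for a mean, n = (1.96×SD)²/d². On the scale of d it says: "For proportion, d is absolute, but for mean, it is relative to the mean".

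The values of p, SD and mean come from two cited studies and are not printed in the article.

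**The concern.** The two places use 3,000 for different quantities. In the abstract it is the number recruited. In the methods it is the number before the attrition allowance, and recruitment is 3,600. The gap is 600 patients. Condensing a longer protocol does not explain it, because both figures stand in the same article.

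Attrition bears on the primary endpoint, which needs the sacubitril/valsartan dose at the end of follow-up as well as at the start. If recruitment stopped at the abstract's figure, the number with an end-of-study dose would fall below the stated target. A reader of the eventual report would also not know which figure to judge recruitment against.

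**Working it through.** **Inputs from the article:** abstract enrolment 3,000; methods target 3,000; attrition about 15%; methods sample size 3,600; precisions 5%, 3% and 2%; z = 1.96. **Assumptions made here:** attrition is exactly 15%, p = 0.5 is the worst case, and patients are independent (no clustering by site).

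**1. The plan's own figure.** Inflating 3,000 for 15% attrition gives 3,000/(1 − 0.15) = 3,529.4, rounded up to 3,530. The stated 3,600 is 70 patients above this (70/3,600 = 1.9%). It corresponds to attrition of 1 − 3,000/3,600 = 16.7%. Since the rate is given only as approximate, 3,600 is reproduced as a conservative rounding up.

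**2. Patients left at the end of follow-up.**
- Enrol 3,000: 3,000 × 0.85 = 2,550, which is 450 below 3,000.
- Enrol 3,600: 3,600 × 0.85 = 3,060, which is 60 above 3,000.

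**3. Worst-case half-width for a proportion**, 1.96 × √(0.25/n):
- n = 2,550: 1.94 points
- n = 3,000: 1.79 points
- n = 3,060: 1.77 points

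**4. Sizes required by the proportion formula at p = 0.5**, 1.96² × 0.25/d²:
- d = 5%: 385
- d = 3%: 1,068
- d = 2%: 2,401

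Both 2,550 and 3,060 exceed 2,401, so 2% precision is kept under either enrolment figure.

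**5. Room for a design effect at 2% precision.** This is 2,550/2,401 = 1.06 if 3,000 are enrolled and 3,060/2,401 = 1.27 if 3,600 are. The article names 200 sites but gives no intra-site correlation, so no design effect can be computed from it. The ratios show only how much margin each enrolment figure leaves.

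**6. The formula for a mean.** As printed, the denominator is d², which is right when d is in the units of the variable. The article lists d as a percentage and defines it relative to the mean. With d as a fraction, the half-width in the variable's units is d × mean, so n = (1.96 × SD/(d × mean))². If d is first converted to a percentage of the mean, the printed formula gives the same answer.

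**The case against.** The strongest reply is that the methods section is explicit, that sites recruit from the full protocol and not from an article's abstract, and that the difference in precision is only 1.94 − 1.77 = 0.17 points, with the 2% level met either way. Most of this stands. The documents do not show that any site would stop at 3,000, and no precision target fails under independence. What remains is that the article assigns 3,000 to two different quantities and that enrolling 3,000 would miss its own target.

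A reader might infer more from the same section. Four such readings are not supported:

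- **That 3,600 is an arithmetic error.** The exact figure at 15% is 3,530, but the rate is given as approximate, and 3,600 is 1.9% higher and on the safe side.
- **That 3,000 conflicts with the stated precision.** The proportion formula never exceeds 2,401 at the listed precisions, but the article calls its results minimum sizes and does not say that 3,000 came from that formula. The formula for a mean gives about 3,000 when SD/mean is about 0.56 (at 2%), 0.84 (at 3%) or 1.40 (at 5%). The inputs are not printed, so this route can be neither confirmed nor excluded. A condensed article may leave the derivation to the full protocol.
- **That the formula for a mean is wrong.** It is correct if d is read as a percentage of the mean already converted to the variable's units. The notation is loose, but nothing shows that the investigators computed it otherwise.
- **That sizing on patient characteristics leaves the primary endpoint without adequate precision.** The inputs are indeed demographic and clinical characteristics, but 3,000 patients give ±1.79 points at worst for any dose-category proportion under independence, which is tighter than the tightest precision listed.

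**Conclusion.** The contradiction between the abstract and the methods is real and should be corrected. It is worth 600 enrolled patients, or 3,060 − 2,550 = 510 evaluable patients at 15% attrition. Only the methods' figure of 3,600 delivers the stated 3,000.

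The statistical consequence is modest: 0.17 points of half-width at worst, with 2% precision kept under both figures. That rests on 15% attrition, p = 0.5 and no clustering by site; a design effect above 1.06 would take the smaller enrolment beyond ±2 points, and one above 1.27 the larger. The notation of the mean formula is a minor clarification.

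**What to change.** - Use one enrolment number and one evaluable number throughout. For example, correct the abstract to say that 3,600 patients will be enrolled so that at least 3,000 remain evaluable after about 15% attrition.
- In the sample size section, state the precision that 3,000 evaluable patients give for the primary endpoint, a dose-category proportion: at worst about ±1.8 points (95% confidence) before any design effect.
- In the same edit, print the formula for a mean as n = (1.96 × SD)²/(d × mean)², so that it agrees with the definition of d as relative to the mean.

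The cost is a text correction. No patients, visits or data items are added to the number already set in the methods.

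### For NYHA class, the default chi-squared test ignores category order as well as pairing, so it can be highly significant with no net improvement; an ordered within-patient summary should be the named default.

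*Protocol article*

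**What the plan says.** The Statistical consideration section gives one rule for all categorical outcomes: "Categorical data (counts and percentages) will be compared between baseline and 12 weeks using the chi-squared test". A parenthesis directly after this leaves room for another test if it is judged suitable. Testing is done "with a two-tailed overall significance level of 0.05". The section names no ordinal method, no measure of change for ordered outcomes and no rule for when the alternative applies. The results are to be given as counts and percentages.

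Under Study treatment, duration, and endpoints, effectiveness is judged on "changes in New York Heart Association (NYHA) functional class and N-terminal pro-B-type natriuretic peptide (NT-proBNP) levels from baseline to follow-up". The Discussion reads NYHA class directionally, linking improvement in class to lower mortality risk.

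On dose, the same endpoint section says: "The primary endpoint of the study is the dosage pattern of ARNI at the start and end of the study". The Discussion adds that the study will "explore the titration to target doses". The article does not say whether dose is handled as a category or as a number.

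**The concern.** NYHA class runs from I to IV, and the clinical question is whether patients moved up or down that scale. Pearson's chi-squared on the table of time by class asks only whether the two distributions differ in any way. Relabelling the classes leaves the statistic unchanged. It also treats baseline and 12 weeks as separate groups of people, although they are the same patients.

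A small p-value from this default, placed beside an effectiveness endpoint, invites the reading that NYHA class improved. The same p-value can arise when equal numbers improved and worsened. At about 3,000 patients almost any redistribution will be significant, so the direction and size of change are what readers need. If ARNI dose is grouped into levels, the same applies to titration.

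**Working it through.** **Inputs from the article.** Target of 3,000 patients; two-sided 0.05; chi-squared as the named default. The article plans 3,600 for about 15% attrition. 3,000/0.85 = 3,530 is close to that, and 3,600 × 0.85 = 3,060, so about 3,000 at follow-up is a fair scale.

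**Inputs assumed.** The article gives no NYHA or dose distribution and no planned figure for this comparison, so every distribution below is an assumption.

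**1. Significant with no net change.** Assume NYHA I–IV of 5/45/45/5% at baseline and 10/40/40/10% at follow-up, with 150 patients moving II→I and 150 moving III→IV.

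| | I | II | III | IV | mean class |
|---|---|---|---|---|---|
| Baseline | 150 | 1,350 | 1,350 | 150 | 2.50 |
| Follow-up | 300 | 1,200 | 1,200 | 300 | 2.50 |
| Expected per row | 225 | 1,275 | 1,275 | 225 | |

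Chi-squared = sum of (observed − expected)²/expected = 4 × 75²/225 + 4 × 75²/1,275 = 100 + 17.65 = 117.65 on 3 df, p = 2.5e-25.

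- Linear trend test on the same table: p = 1.0.
- Sign test, 150 improved against 150 worsened: p = 1.0.
- Net improvement: 5% − 5% = 0, with half-width 1.96 × √(0.10/3,000) = 1.1 percentage points.

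The same percentages with 1,000 patients per time give chi-squared 39.22 (p = 1.6e-8). With 500 they give 19.61 (p = 0.0002). The trend p is 1.0 in both.

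With a milder spread, 5/45/45/5% to 7/43/43/7%, simulation of two independent samples of 3,000 gave rejection in 98.7% of runs for chi-squared and 5.1% for the trend test.

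**2. No direction.** An assumed improvement from 5/55/35/5% to 10/60/27/3% moves mean class from 2.40 to 2.23 and gives chi-squared 102.49. The exact reverse, a worsening, also gives 102.49, and so does reordering the columns. Any two-sided p-value is symmetric in this way. The difference is that an ordered statistic has a sign and an accompanying estimate, and Pearson's statistic has neither.

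**3. Margins do not show individual change.** The follow-up row in step 1 is also reached if, in addition, 300 patients move II→III and 300 move III→II. Then 450 improved and 450 worsened (15% each) instead of 150 and 150 (5% each). Counts and percentages by class are identical in the two cases.

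**4. Pairing alone does not cure it.** Assume 0/60/35/5% at baseline, with 300 patients moving II→I, 150 moving II→III and 150 moving III→IV. Follow-up is 10/45/35/10%, mean class is 2.45 at both times, and 300 improved against 300 worsened. Pearson chi-squared = 300 + 64.3 + 0 + 50 = 414.3. The paired nominal test (Stuart-Maxwell) = 300²/300 + 150²/150 + 150²/150 = 600 on 3 df. Both reject overwhelmingly with zero net change.

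**5. Dose, if grouped in three ordered levels.** Assume 30/50/20% to 35/40/25%, with mean level 1.90 at both times. Chi-squared = 11.54 + 33.33 + 16.67 = 61.54 on 2 df, p = 4.3e-14. Trend p = 1.0; Mann-Whitney p = 0.72.

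**6. Cost when the shift is real but small.** For 5/55/35/5% to 6/57/32.5/4.5% with 3,000 per time, simulated power was 61% for chi-squared and 74% for the trend test, again treating the two times as independent samples.

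**The case against.** The strongest reply is that the sentence does not bind the analyst to chi-squared. It allows any other suitable test, and a condensed article may leave the choice for each endpoint to a fuller document. That stands against any claim that the plan excludes an ordinal analysis, or that the study cannot answer its effectiveness question. It does not remove the point that the only method named fits this endpoint poorly and that nothing says when to leave it.

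Second, counts and percentages will accompany the test, so readers will see the marginal direction and size. This is correct. The lack of direction belongs to the test, not to the whole planned report. What the margins leave out is how many individual patients improved or worsened (step 3).

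Third, the illustrations are constructed. If most changes run one way, chi-squared and an ordered test will usually agree at this sample size. This also stands: the examples show possibility, not expectation.

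Fourth, the more basic fault in the sentence is treating the same patients as independent groups, and the remedy overlaps with that correction. The overlap is real, but step 4 shows that a paired nominal test would leave the ordering problem in place.

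Two stronger readings are tempting and are not supported:

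- From "The study population will consist of symptomatic chronic HFrEF patients" a reader might infer that class I is empty at baseline by construction. The article refers to cited criteria and states no NYHA range for entry. Step 1 does not need an empty class I; step 4 uses it only as an assumption.
- A reader might take the primary dose endpoint as certainly affected. That holds only if dose is analysed as ordered levels, which the article does not say.

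**Conclusion.** The point holds for NYHA class as a badly chosen default, not as a plan that rules out a sound analysis. The one named test ignores both order and pairing. Under the assumed symmetric spread with 3,000 patients per time it returns p of about 2.5e-25, where trend and sign tests return 1.0 and net improvement is 0 ± 1.1 percentage points. These figures rest on assumed distributions and transitions. For ARNI dose the point is conditional on dose being treated as ordered categories. The matter is worth correcting because the remedy is nearly free and the risk is that a p-value without direction is read as effectiveness.

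**What to change.** In the Statistical consideration section, name the default for ordered outcomes. For NYHA class, and for ARNI dose if it is analysed as ordered levels, report within-patient change: the share improved (or up-titrated) by at least one step, the share unchanged, the share worsened (or down-titrated), and the net difference with a 95% CI. If a test is wanted, name the Wilcoxon signed-rank test or the sign test.

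Make this edit together with the pairing correction to the same sentence. A trend or Mann-Whitney test on the unpaired table would respect order but not pairing, and Stuart-Maxwell the reverse.

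The cost is one or two sentences. Change in NYHA class is already an endpoint, and medication dose and titration are already recorded at baseline and at the end, so no new data or patients are needed.
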